#### Recruitment

Participants will be identified through specialist referral and through oncology multidisciplinary team meetings. Plastic surgeons and head and neck surgeons are well informed of the trial in our institution as most referrals would come from them. We will also advocate for patients to be treated with CRIO if surgery entails mutilating surgery such as cranio-facial resection which will result in significant functional and cosmetic morbidities.

### Assignment of interventions: allocation

#### Sequence generation

Not applicable. All patients in this trial will receive the same treatment.

#### Concealment mechanism

Not applicable. All patients will receive the same treatment.

#### Implementation

Not applicable. All patients will receive the same treatment.

### Assignment of interventions: blinding

#### Who will be blinded

Not applicable. All patients will receive the same treatment.

#### Procedure for unblinding if needed

Not applicable. All patients will receive the same treatment.

### Data collection and management

#### Plans for assessment and collection of outcomes

As per schedule of assessments (Table 1). All treatment related toxicities will be recorded at each clinic visit for a total of two years in the Case Report Form using the CTCAE 4.03. (https://evs.nci.nih.gov/ftp1/CTCAE/CTCAE_4.03_2010-06-14_QuickReference_8.5x11.pdf).

Disease status of patients will be recorded at each visit during and after completion of treatment.

#### Plans to promote participant retention and complete follow-up

Prior to study entry screening will be conducted by trial staff and will include consideration of the ability for the participant to complete treatment and follow-up. A participant is free to withdraw from this project at any stage and have the option to request for trial biological samples to be disposed of.

#### Data management

Only re-identifiable trial data will be stored in a password protected trial database. Trained, registered personnel will have access to the trial database via password protected login. All hardcopy (paper] data will be kept behind locked doors or in locked cabinets in the trial coordinator's room.

### Confidentiality

#### Patient confidentiality

The Investigator must ensure that the patient's privacy is maintained. A patient should only be identified by the unit code and his / her patient identifier on the case report forms or other documents submitted to the Data Agency. Only re-identifiable trial data will be stored.

#### Plans for collection, laboratory evaluation and storage of biological specimens for genetic or molecular analysis in this trial/future use

Translational studies will include analyses of tumour tissue and peripheral blood samples from participants (the biospecimens). This includes formalin-fixed, paraffin-embedded tumour tissue obtained at baseline (pre-treatment) and peripheral blood before and/or after treatment. Patients will be invited to undergo a repeat core biopsy of the gross disease at 2 weeks into the treatment. Participation for the repeat biopsy is optional. The rationale for the repeat biopsy is to explore if there are any interim biomarkers with treatment response. Peripheral blood will be transported to the central laboratory within 1 h of collection and processed with serum and peripheral blood mononuclear cells stored for future analysis when the trial is complete. Immune markers of interest will be assessed via multiplex immunohistochemistry for formalin-fixed, paraffin-embedded tumour samples or flow cytometry on peripheral blood mononuclear cells. The peripheral blood mononuclear cells will be stored in liquid nitrogen.

### Statistical methods

#### Statistical methods for primary and secondary outcomes

For the first stage, the analysis will focus on descriptive statistics. Categorical variables will be summarised using frequencies and percentages and continuous variables will be summarised using means with standard deviations or as medians with interquartile ranges. Median survival time (with 95% CI) will be described and survival time will be presented using a Kaplan–Meier curve. Safety/toxicity data will be presented according to the frequency of occurrence. The proportion of patients experiencing the primary outcome (complete response) will be presented with 95% confidence intervals and compared to the hypothesized null effect of 0.5 using an exact binomial test.

Secondary outcomes including overall survival, disease free survival, time to progression and loco-regional control will be presented using a Kaplan–Meier curve.

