**Methods:**

Patients with unresectable locally and or regionally advanced pathologically confirmed cSCC (stage III-IVa) deemed fit for CRIO by consensus of the Multidisciplinary meeting will be eligible. In the first stage of a two-stage minimax design, we aim to recruit a total of 15 patients. If fewer than 7 patients achieved a complete response in the first stage, we will conclude the treatment is not more effective than standard treatment. The co-primary endpoints of CRIO are the safety of treatment (acute and late toxicities) and the rate of complete response. Secondary endpoints would include overall survival, progression free survival, and locoregional control. Translational research endpoints including biomarkers (CD73, CD39, PD-1, PD-L1) will also be explored utilising multiplex immunohistochemistry on tumour biopsy samples obtained prior to commencing treatment and during treatment (week 2). In addition, the utility of CXCR-4 PET/CT scan will be explored.

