#### Sample size

A two-stage minimax design will be applied, which requires an initial sample of 15 patients, with possibly an additional 13 patients required (total 28) subject to feasibility. The hypothesis that the proportion responding is 70% or more compared to the alternative hypothesis that 50% or fewer respond will be tested using a two sided binomial test with a target significance level of 0.10 and power of 0.80. Fifteen patients would be recruited in the first stage and if 7 or fewer patients respond the trial will be terminated and we will conclude that the treatment is not more effective than standard treatment. If 8 or more patients respond, the trial may go to the second stage, recruiting a further 13 patients. Of the total of 28 patients, 18 or more must respond to the treatment to be considered better than current treatment. Sample size was calculated using the PASS 13 Power Analysis and Sample Size Software (NCSS, 2014).

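### The stated analysis of complete response does not allow for the futility gate at 15 patients or say which stage it covers; the effect is small and changes no success verdict

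*Protocol article*

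**What the plan says.** All references are to the Protocol article.

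- **Sample size**, stage sizes: the design "requires an initial sample of 15 patients, with possibly an additional 13 patients required (total 28) subject to feasibility".
- **Sample size**, gate: "if 7 or fewer patients respond the trial will be terminated"; otherwise, "If 8 or more patients respond, the trial may go to the second stage, recruiting a further 13 patients".
- **Sample size**, success rule: "Of the total of 28 patients, 18 or more must respond to the treatment to be considered better than current treatment".
- **Abstract, Methods**, a different gate: the treatment is judged no better than standard "If fewer than 7 patients achieved a complete response in the first stage".
- **Statistical methods for primary and secondary outcomes**: the complete-response proportion "will be presented with 95% confidence intervals and compared to the hypothesized null effect of 0.5 using an exact binomial test". The interval method and the sidedness of the test are not given here. The paragraph begins by confining itself to the first stage, and no separate text covers the 28-patient analysis.
- **Interim analyses**: none is foreseen, so the gate does not appear in the analysis text.

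**The concern.** With a gate at 15 patients, the final count out of 28 is not an ordinary binomial count, because totals that follow a poor first stage are never observed. A plain exact binomial analysis treats 28 as fixed in advance. The observed rate is then not exactly unbiased, and the plain p-value is not the probability on which the design's error rate rests. Complete response is the trial's efficacy answer and the figure a later trial would plan from, so it is worth knowing how far the reported rate, interval and p-value could mislead.

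**Working it through.** **Inputs (Sample size section).** Null rate 0.50 and target rate 0.70; n1 = 15, n2 = 13, n = 28; stop at 7 or fewer of 15; success at 18 or more of 28.

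**1. Reproduce the design.** Let A(k, p) be the chance of passing the gate and ending with at least k responders:

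A(k, p) = Σ (x = 8 to 15) Bin(x; 15, p) × P(Y ≥ k − x), with Y ~ Bin(13, p).

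A(18, 0.5) = 0.0900 and A(18, 0.7) = 0.8009. The chance of stopping at stage 1 is 0.500 at a true rate of 50% and 0.050 at 70%. A minimax search at one-sided 0.10 with power 0.80 returns exactly this design.

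**2. Plain against two-stage p-value.** The plain one-sided p is P(T ≥ k), with T ~ Bin(28, 0.5). The two-stage p is A(k, 0.5). Passing the gate and reaching k is a subset of reaching k, so the two-stage p can never be the larger.

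**3. Bias of the observed rate (x/15 if stopped, x/28 if not).** Bias = P(stop) × (mean of x/15 when stopped − p) + P(continue) × (mean of x/28 when continued − p).

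- p = 0.5: 0.500 × (0.3953 − 0.5) + 0.500 × 0.0561 = −0.024
- p = 0.6: 0.213 × (0.4227 − 0.6) + 0.787 × 0.0257 = −0.018
- p = 0.7: 0.050 × (0.4404 − 0.7) + 0.950 × 0.0073 = −0.006

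The largest value for p between 0.30 and 0.90 is −0.024. The last term in each line gives the bias among trials that reach 28 patients: +5.6, +2.6 and +0.7 points.

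**4. Unbiased estimate and interval.** For a total t at stage 2, UMVUE = Σ C(14, x−1) C(13, t−x) / Σ C(15, x) C(13, t−x), summed over the stage 1 counts x of 8 or more that are compatible with t. The two-stage 95% limits solve A(k, p) = 0.025 (lower) and A(k+1, p) = 0.975 (upper). The plain interval is taken to be Clopper-Pearson, which is an assumption.

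| Responders of 28 | x/28 | UMVUE | Plain p | Two-stage p | Plain 95% CI | Two-stage 95% CI |
|---|---|---|---|---|---|---|
| 14 | 50.0% | 57.3% | 0.575 | 0.418 | 30.6–69.4% | 32.6–73.9% |
| 15 | 53.6% | 58.7% | 0.425 | 0.343 | 33.9–72.5% | 35.1–74.8% |
| 16 | 57.1% | 60.4% | 0.286 | 0.251 | 37.2–75.5% | 37.8–76.5% |
| 17 | 60.7% | 62.5% | 0.173 | 0.162 | 40.6–78.5% | 40.9–78.8% |
| 18 | 64.3% | 65.1% | 0.0925 | 0.0900 | 44.1–81.4% | 44.2–81.4% |
| 20 | 71.4% | 71.5% | 0.0178 | 0.0178 | 51.3–86.8% | 51.3–86.8% |

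Both p-values exceed 0.10 at 17 and fall below it at 18.

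**5. Coverage.** With the gate in force, the Clopper-Pearson 95% interval covers at least 0.949 (mean 0.970) for p from 0.30 to 0.90. With a fixed 28 patients the figures are 0.952 and 0.969.

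**6. How often the affected results occur.** The chance of passing the gate and ending at 17 or fewer is 41%, 40% and 15% at true rates of 50, 60 and 70%. For 14 or fewer it is 16%, 7% and 1%.

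**7. Sensitivity to the abstract's gate (stop at 6 or fewer).** The bias becomes −2.1, −1.0 and −0.2 points at 50, 60 and 70%. At 14/28 the UMVUE is 53.6% and the two-stage upper limit 70.7%. At 18/28 the two-stage p is 0.0922. The adjusted figures therefore depend on which gate applies.

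**The case against.** The strongest reply is that nothing is broken. The only early stop is for futility, which cannot raise the type I error, and step 2 shows that the plain one-sided p errs on the safe side. This stands. A reader might infer that the reported test or interval is invalid, or that the trial's verdict is at risk; the documents do not support either.

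The second reply concerns direction. A reader might infer that x/28 is too pessimistic for a trial that continues. It is low only when averaged with stopped trials. Among trials that reach 28 patients it is already high on average, and the UMVUE is higher still: +10.5 points against +5.6 at a true rate of 50%. Nor is the UMVUE uniformly more accurate: at 50% its root-mean-square error is 0.121 against 0.113, although it does slightly better at 60 and 70%. This also stands, so the UMVUE belongs beside x/28 and not in its place.

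Third, at 14/28 the plain interval excludes 70% and the two-stage one does not. That is the most favourable example in the table. At a true rate of 70% that exact result has probability 0.65%, and the trial fails by four responses whichever interval is used.

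Fourth, the sentence may concern only the first 15 patients, for whom plain formulas are suitable, and the choice of interval could sit in an analysis plan not shown. This stands in part: the text does name a plain exact test, and if it is meant for stage 1 only, the article states no analysis for 28 patients.

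A mismatch of more consequence is separate. The test is described as a "two sided binomial test with a target significance level of 0.10 and power of 0.80", yet the boundaries correspond to one-sided 0.10, so 18/28 meets the count rule while its two-sided exact p is 0.185. The present point remains after that is settled.

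**Conclusion.** The point holds as a minor one of estimation and wording. The stated analysis does not reflect the design's gate and does not say which stage it covers. If it is applied to 28 patients, the cost is an overall downward bias of at most 2.4 points. From 18/28 upward the estimate moves by less than 1 point, the limits by about 0.001 and the one-sided p by at most 0.0025. Differences large enough to notice are confined to failed trials, chiefly 14 to 17 of 28, where the UMVUE exceeds x/28 by 7.3 down to 1.8 points. Lower totals differ more but are less likely.

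These figures assume the Sample size section's gate, continuation whenever 8 or more respond (the text says only that the trial may continue), every patient counted in the denominator, one-sided p-values, and a Clopper-Pearson interval as the plain comparator.

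**What to change.** In Statistical methods for primary and secondary outcomes:

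1. State whether the complete-response sentence covers the 15-patient result, the 28-patient result or both.
2. Reconcile the stage 1 cut-off between the Abstract and the Sample size section. No two-stage p-value or interval is defined until there is one gate.
3. For a trial that reaches 28 patients, keep x/28 and add the two-stage p-value A(k, 0.5), the 95% interval from inverting the same probability (Koyama-Chen), and the UMVUE (Jung-Kim) as a supplementary estimate. Note that the UMVUE is unbiased only over all outcomes, stopped trials included.
4. For a stop at stage 1, report x/15 with its exact interval and note that the stopping rule makes it low on average.

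The cost is one paragraph and a few lines of code, with no extra patients or data. The downside is slightly more analysis and two estimates to explain to readers.

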#### Interim analyses

No interim analysis is planned. The sample size in this study is small.

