### Oversight and monitoring

#### Composition of the coordinating centre and trial steering committee

Metro North hospital and health service (Queensland, Australia) has the overall responsibility to initiate and conduct the CRIO study and has designated responsibility to the Principal Investigator for the day-to-day conduct of the study and to lead, train and supervise study site staff. Astra Zeneca will collaborate to support the study as detailed in the research agreement.

This trial is reviewed by a data safety monitoring committee every 6 months to review safety and efficacy aspects of the trial,

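### The plan says there is no interim analysis but makes a stop/go decision at 15 patients, and it defines no conclusion if the trial ends there with 8 or more responders

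*Protocol article*

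**What the plan says.** All references are to the protocol article.

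- *Interim analyses*: "No interim analysis is planned. The sample size in this study is small".
- *Sample size*: a two-stage minimax design with 15 patients first; "if 7 or fewer patients respond the trial will be terminated". With 8 or more responders the trial may, but need not, continue: the design comes "with possibly an additional 13 patients required (total 28) subject to feasibility". Success is defined only at the end, as 18 or more responders among 28. The error rates are those of a "two sided binomial test with a target significance level of 0.10 and power of 0.80".
- *Statistical methods for primary and secondary outcomes*: the paragraph begins "For the first stage, the analysis will focus on descriptive statistics". Later in the same paragraph the complete response (CR) proportion is to be "compared to the hypothesized null effect of 0.5 using an exact binomial test". No stage is attached to that test.
- *Participant timeline*: a two-year accrual period is given for 15 patients, and none for 28.
- *Abstract, Methods*: the stage-1 stopping threshold is given as fewer than 7 responders, one lower than in *Sample size*.

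**The concern.** A pre-specified stop/go decision on the primary endpoint after 15 patients is an interim analysis, whatever the sample size. The statement that none is planned is therefore wrong on the face of the document.

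The larger problem is what follows a pass at stage 1. The plan leaves stage 2 open and gives an accrual period only for 15, so ending at 15 is a realistic outcome. If it happens with 8 or more responders, the futility rule has not been met and the success rule cannot be applied. The only inference left is an exact test whose stage is unspecified. What may be claimed would then be decided after the responses are known, and the quoted power of 0.80 would describe a trial that was not run.

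**Working it through.** **Inputs.** Null CR rate p0 = 0.50 and target rate p1 = 0.70, from *Sample size*. That sentence reads "The hypothesis that the proportion responding is 70% or more compared to the alternative hypothesis that 50% or fewer respond", with the two labels reversed; *Statistical methods* confirms 0.5 as the null. Stage 1 has n1 = 15 and stops at 7 or fewer; stage 2 adds 13; success is 18 or more of 28.

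**1. Reproduce the stated design.** The probability of declaring success is

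S(p) = Σ (x = 8 to 15) C(15,x) p^x (1−p)^(15−x) × P[Bin(13,p) ≥ 18−x].

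- S(0.50) = 0.0900 (one-sided type I error).
- S(0.70) = 0.8009 (power).
- Probability of stopping at stage 1: 0.50 under p0 and 0.05 under p1.

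An exhaustive minimax search at one-sided 0.10 and power 0.80 returns exactly this design: 15, stop at 7 or fewer, 28, success at 18. The design is therefore sound, but it is one-sided, and S(p) assumes that stage 2 is always run after 8 or more responders.

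**2. How often the undefined state can arise.** P(8 or more of 15) is 0.50 at p0 and 0.95 at p1. Each such trial has no defined conclusion if stage 2 is not opened.

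**3. Trial ends at 15 and the exact test is used.**

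- 11 of 15: one-sided p = (1365+455+105+15+1)/32768 = 0.0592, two-sided p = 0.118. It is significant at one-sided 0.10 but not at two-sided 0.10. Power at 0.70 is 0.515.
- 12 of 15: one-sided p = (455+105+15+1)/32768 = 0.0176, two-sided p = 0.035. This is the threshold at two-sided 0.10. Power at 0.70 is 0.297.

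**4. Stage 2 sometimes not opened.** Let q be the probability that a trial with 8 or more responders is halted at 15 for feasibility, independently of the result. The documents give no q, so a range is shown. Success probability is (1−q)·S(p) + q·P(X1 ≥ c), where c is the threshold applied at 15; the last column has no claim at 15. Entries are type I error / power.

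| q | c = 12 | c = 11 | no claim |
|---|---|---|---|
| 0 | 0.090 / 0.801 | 0.090 / 0.801 | 0.090 / 0.801 |
| 0.25 | 0.072 / 0.675 | 0.082 / 0.730 | 0.068 / 0.601 |
| 0.50 | 0.054 / 0.549 | 0.075 / 0.658 | 0.045 / 0.400 |
| 1 | 0.018 / 0.297 | 0.059 / 0.515 | 0 / 0 |

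Type I error falls as q rises, and so does power.

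**5. A stage-1 test counted as an extra route to success, with the trial otherwise continuing.** For x ≥ c, replace the stage-2 tail by 1 in the sum for S(p).

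- c = 11 (one-sided threshold): type I error 0.1153, power 0.818.
- c = 12 (two-sided threshold): type I error 0.0945, power 0.804.

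**6. Sidedness of the final rule.** P[Bin(28, 0.5) ≥ 18] = 0.0925, so 18 of 28 passes a one-sided 0.10 test. Doubled, p = 0.185, which fails a two-sided 0.10 test; 19 responders are needed (two-sided p = 0.087).

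**7. The two stage-1 thresholds.** Stopping at 6 or fewer, as the abstract implies, gives 0.0922 / 0.808. The error rates hardly move, but the chance of stopping under p0 drops from 0.50 to 0.30.

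**The case against.** The strongest reply is that *Sample size* gives both the stage-1 rule and the final rule in numbers, so nobody running the trial would be unsure what to do at 15. On this view, the *Interim analyses* sentence means only that there is no look beyond the two-stage rule. That is a possible intention, but it is not what the sentence says, and it does not supply a conclusion for a trial that ends at 15.

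Other parts of the reply do stand and limit the point:

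- A reader might infer that the stated 0.10 and 0.80 are wrong for this design. They are not; the two-stage rule gives 0.090 and 0.801. A futility-only look does not raise type I error, and ending at 15 under an exact test lowers it.
- A reader might infer that type I error exceeds 0.10. The figure of 0.115 needs a one-sided threshold of 11 and a stage-1 result counted as success. The plan provides for neither: it calls the test two-sided, which gives 0.0945, and defines success only at 28.
- A reader might infer that the plan tests the stage-1 data. The paragraph opens with stage 1 and calls that analysis descriptive; the test sentence names no stage. The supportable complaint is ambiguity.
- A reader might infer that 8 of 15 is treated as success. The plan treats it only as permission to continue.
- The six-monthly "data safety monitoring committee every 6 months to review safety and efficacy aspects of the trial" has no stated efficacy rule, but such rules commonly sit in a charter or the full protocol, so this is no finding.

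**Conclusion.** The point holds as a contradiction and a missing decision rule. The statement that no interim analysis is planned conflicts with the binding futility decision at 15, and a trial that ends at 15 with 8 or more responders has no defined conclusion. The stated error rates apply only if stage 2 always follows a pass at stage 1. If the trial ends at 15, power against 0.70 is 0.30 or 0.52 by the exact test, depending on sidedness, and zero if no claim is made. The cost is lost power and an interpretation left open; a general inflation of type I error is not shown. These results take each patient's response as binary and independent. The intermediate power figures also rest on the assumed q.

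**What to change.** 1. *Interim analyses*: replace the statement with one that names the look at 15 patients as the single planned analysis before the end, for futility only. Use the same patient set as the primary analysis. That set needs to be explicit, because the analysis is intention-to-treat with all patients included, while patients with large nerve perineural spread are stated not to be assessable for CR.
2. Reconcile the stage-1 threshold in the abstract with that in *Sample size*. The latter is the one that reproduces as the minimax design.
3. *Statistical methods*: state that stage 1 is descriptive, with the CR rate and its confidence interval, and that the test against 0.5 is made only at 28 patients, consistently with the 18-of-28 rule.
4. *Sample size*: correct the two-sided label to one-sided. Keeping two-sided 0.10 with power 0.80 would call for a different minimax design (23 then 37 patients, success at 24 or more).
5. State that if the trial ends at 15 with 8 or more responders, the CR rate is reported with its confidence interval, superiority over 50% is not claimed, and the 0.80 power does not apply.

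No change to the monitoring committee's remit is needed. The changes add no patients if the one-sided design is kept. The cost is giving up any significance claim from 15 patients.
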